### Outcome measures

The primary outcome and its definition are described in detail below. Pre-specified secondary outcomes are presented in Table 2 below, each with its definition, instrument or data source, timing of ascertainment, and analytic role.

**Table 2 pone.0356813.t002:** Pre-specified primary and secondary outcomes.

Outcome	Definition	Instrument / Data Source	Timing of Ascertainment	Priority	Analytic Role
**Time to fecal continence**	First clinic visit (confirmed at subsequent visit) at which the participant meets social continence threshold: BCS criteria (ARM) or BFS ≥ 17 (HD), from date of definitive repair	BCS (ARM) [16] or BFS (HD) [17], parent/caregiver proxy to age 11; self-report from age 12	Annual visits from age 3	**PRIMARY**	Kaplan–Meier estimation; Cox proportional hazards regression; Fine-Gray model for competing risks; landmark analyses at ages 5 and 10
HD-associated enterocolitis (HAEC)	≥1 physician-confirmed episode meeting Ruttenstock criteria requiring medical treatment	Clinical record review; REDCap adverse event log	Each annual visit; first episode date recorded	Secondary 1	Cox regression / Fine-Gray competing risks; descriptive incidence rate
Reoperation rate	Any unplanned surgical return to the operating room following index repair	Operative report review; REDCap surgical procedure log	Cumulative from index repair; each annual visit	Secondary 2	Cox regression / Fine-Gray competing risks; cumulative incidence curve
Disease-specific quality of life	HAQL total score and subscale scores (age-appropriate version)	HAQL questionnaire, self- or proxy-report [18]	Ages 6, 10, and 14 years	Secondary 3	Linear mixed-effects model (repeated measures); descriptive means by group
Transition readiness	Transition Readiness Assessment Questionnaire	TRAQ [19], self-report	Ages 14 and 17 years	Secondary 4	Linear mixed-effects model; descriptive score trajectory
Loss to follow-up (LTFU)	No clinic encounter, survey, or successful contact for ≥18 months while under age 18 and not yet transitioned	REDCap contact log; clinic attendance record	Flagged at 18-month mark; reviewed at each annual analysis	Secondary 5	Logistic regression (ever-lost vs retained); descriptive LTFU rate

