The primary outcome is time to achievement of fecal continence from the date of definitive surgical repair, analysed as a time-to-event outcome. For participants with ARM, continence is assessed using the Baylor Continence Scale (BCS) [16], with social continence defined as no soiling episodes in the preceding 4 weeks per published BCS criteria, completed by the parent or caregiver proxy up to age 11 and by self-report from age 12. For participants with HD, continence is assessed using the Bowel Function Score (BFS) [17], with social continence defined as a BFS score ≥ 17, administered to the parent or caregiver proxy up to age 11 and by self-report from age 12. Both instruments are administered at every annual clinic visit beginning at age 3 years. The earliest clinically meaningful assessment for continence is age 3, consistent with normal developmental milestones for voluntary bowel control. Participants will be censored at age 18, death, transition to adult care, or loss to follow-up, whichever occurs first.

Pre-specified secondary outcomes, listed in priority order, are: (1) Hirschsprung-associated enterocolitis (HAEC), defined as at least one physician-confirmed episode meeting the Ruttenstock diagnostic criteria and requiring medical treatment, assessed at each annual visit [20]; (2) reoperation rate, defined as any unplanned surgical return to the operating room following index repair, assessed cumulatively; (3) disease-specific quality of life, measured using the HAQL [18] at ages 6, 10, and 14 years using age-appropriate versions; (4) transition readiness, assessed at ages 14 and 17 years using the validated Transition Readiness Assessment Questionnaire (TRAQ) [19], and (5) loss to follow-up rate, defined operationally in the Loss to Follow-Up section. Each secondary outcome will be reported descriptively and, where the events-per-variable threshold is met (see Sample Size section), included as an endpoint in pre-specified multivariable analyses with the analytic role specified in the Statistical Analysis section.

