### Loss to Follow-Up

A participant will be considered lost to follow-up if there has been no clinic encounter, completed survey, or successful contact (by telephone, email, or mail) for 18 or more consecutive months in a participant aged under 18 years who has not yet transitioned to adult care or withdrawn from the registry.

When a participant misses a scheduled visit without prior notification, the research assistant will initiate a standardised re-contact sequence: (1) two phone call attempts within 2 weeks; (2) email or written letter within 4 weeks, if contact information is on file; and (3) two further phone call attempts at 3 months. If no successful contact is made after this full sequence, the participant will be flagged as lost to follow-up in REDCap with the date of last confirmed contact recorded. All contact attempts and outcomes will be logged prospectively.

Rates and timing will be reported descriptively at each annual analysis. In survival and longitudinal analyses, the loss will be treated as censoring at the date of last confirmed contact. The potential impact of informative (non-random) censoring will be examined using inverse probability weighting (IPW) as a sensitivity analysis [26,27]. Factors independently associated with the loss will be examined using logistic regression (ever-lost vs retained) as a secondary analysis, with candidate predictors pre-specified to include: diagnosis type, age at enrollment, sex, aganglionosis length or ARM Krickenbeck category, area-level deprivation quintile, and distance from COCOE.

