### Survey administration and burden mitigation

The six instruments have a combined estimated completion time of 54–95 minutes depending on age and programme status. To reduce burden, instruments are administered in a staggered fashion across visits: the HAQL, BCS and BFS are prioritised at each visit; the PedsQL modules and PECI are administered at alternating annual visits; and the PREOM-BMP is administered only to eligible families. Where possible, surveys are distributed electronically via REDCap prior to the clinic visit to allow completion at home, reducing in-clinic time. Paper versions are available for families without internet access, and a trained research assistant is available to assist with completion where literacy or language is a barrier. Surveys are available in English and French. In the event of partial completion, available items will be scored according to the instrument's published scoring guidelines; instruments with fewer than the minimum required items completed will be recorded as missing and addressed per the missing data plan in the Statistical Analysis section. Based on experience from comparable paediatric surgical registries, we anticipate an instrument completion rate of approximately 70–80% per visit; completion rates will be reported at each annual analysis.

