**Objective 3:** Factors associated with key outcomes. Time to achievement of fecal continence will be estimated using the Kaplan–Meier method, with curves reported separately for ARM and HD given the use of disease-specific instruments. Given the embryological, surgical, and prognostic distinctions between the two conditions, and the use of disease-specific continence instruments, multivariable analyses will be conducted separately for ARM and HD rather than as a single combined model. For each disease cohort, a Cox proportional hazards model will be fitted with disease-appropriate pre-specified candidate predictors: for ARM, Krickenbeck category, age at index repair, sex, syndromic status, and area-level deprivation quintile; for HD, length of aganglionosis, age at index repair, sex, syndromic status, and area-level deprivation quintile. The proportional hazards assumption will be tested for each model using Schoenfeld residuals. Where competing risks are present (death or transition prior to the continence event), the Fine-Gray subdistribution hazard model will be applied within each cohort. Pre-specified landmark analyses will report the proportions achieving continence by age 5 and age 10 for each disease, to allow benchmarking against published ARM and HD cohort data. For each disease-specific model, multivariable Cox regression will be triggered only once the events-per-variable (EPV) threshold of 10 is met within that cohort at interim review; otherwise analyses for that cohort will be limited to descriptive and unadjusted comparisons.

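### Loss to follow-up is censored at the last contact, but continence is known only up to the last BCS/BFS, so contact-only time counts as continence-free and lowers the continence curve

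*Protocol article*

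**What the plan says.** **Event.** Table 2 (Outcome measures) defines the primary event as "First clinic visit (confirmed at subsequent visit) at which the participant meets social continence threshold": the BCS criteria for ARM, BFS ≥ 17 for HD. The text below the table adds that "Both instruments are administered at every annual clinic visit beginning at age 3 years".

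**Follow-up.** The Loss to Follow-Up section calls a child lost after "no clinic encounter, completed survey, or successful contact (by telephone, email, or mail) for 18 or more consecutive months". Table 2 repeats the rule: "No clinic encounter, survey, or successful contact for ≥18 months while under age 18 and not yet transitioned". A telephone call without any assessment is therefore enough to keep a child in follow-up.

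**Censoring.** Outcome measures states: "Participants will be censored at age 18, death, transition to adult care, or loss to follow-up, whichever occurs first". Loss to Follow-Up supplies the date for loss: "the loss will be treated as censoring at the date of last confirmed contact".

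**Analysis.** Under Objective 3 in Statistical analysis, "Time to achievement of fecal continence will be estimated using the Kaplan–Meier method", separately for ARM and HD, with Cox models and landmark proportions at ages 5 and 10. Nowhere is the censoring date tied to the last BCS or BFS, and no interval-censored analysis is planned.

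**The concern.** Event and follow-up run on different clocks. A child can be seen to become continent only when a scorable BCS or BFS is obtained, but is counted at risk for as long as someone reaches the family. When a visit is missed without notice, the re-contact sequence starts. One answered call then resets the 18-month clock. A family that answers calls but does not come back for assessment stays in the denominator with no chance of contributing an event.

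The age-10 landmark is at stake, since it is meant for benchmarking against published ARM and HD cohorts. The adjusted results are at stake too: deprivation quintile is a pre-specified predictor in both Cox models, so if contact-only follow-up is commoner in some quintiles, that coefficient absorbs part of the artefact.

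**Working it through.** **The plan's own figures.** The article gives no figure for the censoring rule. Its nearest figures are the projected events: 0.30 × 480 = 144 and 0.35 × 680 = 238, against 145–240 stated, or about 14–24 covariates at 10 events per variable. These reproduce.

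**Direction.** Each Kaplan–Meier step multiplies the continence-free proportion by 1 − d/n. For children who do not return, moving censoring from last assessment to last contact leaves every d unchanged and can only enlarge n. Cumulative continence is therefore equal or lower at every age.

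**Hand example (assumed inputs).** Start with 100 children. Each year 10% of those assessed become continent, and 20% of those remaining after year 1 become contact-only.

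- Year 1: 10/100 under both rules. Of the 90 left, 18 become contact-only and 72 stay assessed.
- Year 2: 7.2/72 = 0.100 (last assessment) against 7.2/90 = 0.080 (last contact).
- Years 3 to 5: 0.100 each year, against 6.48/82.8, 5.832/76.32 and 5.2488/70.488.
- At 5 years: 1 − 0.9⁵ = 41.0% against 34.8%.

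**Age-10 landmark, families reachable indefinitely.** Assumptions: continence onset spread evenly over ages 3–11 in a share q of children; annual visits with full completion; from age 4, a share p per year becomes contact-only for good, unrelated to continence; age as the time scale; confirmation ignored for now. The true proportion at age 10 is q × 7/8, which is 30.6% for q = 0.35 and 43.8% for q = 0.50. As nobody without an event leaves the risk set before age 10, the estimate is (q/8) × Σ(1 − p)^j for j = 1 to 7. The sum is 6.21, 5.73 and 4.70 for p = 3%, 5% and 10%.

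| p per year | contact-only by age 10, 1 − (1 − p)⁷ | true 30.6% estimated as | true 43.8% estimated as |
|---|---|---|---|
| 3% | 19% | 27.2% | 38.8% |
| 5% | 30% | 25.1% | 35.8% |
| 10% | 52% | 20.5% | 29.3% |

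The loss is 3.5 to 10.1 points for the first column and 5.0 to 14.5 for the second.

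**Same model, contact-only time averaging 2 years (simulated).** The true 31% is estimated as 29.5%, 28.8% and 26.8%; the true 44% as 42.5%, 41% and 39%. Depending on how contact-only time is distributed, the loss is about 1–5 points for 31% and 2–6 points for 44%.

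**A second simulation, with the confirmation rule and 75% completion.** Constant continence hazard of 0.05 per year from age 3; completion taken from the article's 70–80%; all other inputs assumed.

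| stop clinic per year | share still reachable | mean contact-only years | censored at last BCS/BFS, age 10 | censored at last contact, age 10 |
|---|---|---|---|---|
| 5% | half | 2 | 25.7% | 24.3% |
| 10% | half | 3 | 25.0% | 21.7% |
| 10% | all | 3 | 25.4% | 20.0% |
| 15% | all | 5 | 24.9% | 15.7% |

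At a hazard of 0.08 the range runs from 37.7% against 35.8% to 35.9% against 22.7%. At age 5 the gap is 0.2–1.1 points (hazard 0.05) or 0.4–1.7 points (hazard 0.08).

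**Does last-assessment censoring alone repair it?** In the first model without confirmation it returns 31% and 44%. With confirmation required and the event dated at the first positive, it returns about 28–30% against 31%, and 40–43% against 44%, because a positive at the last assessment is censored as a non-event. If continent children also stop attending twice as often (assumed), it returns about 28%, 27% and 23% against 31%.

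**The case against.** **The size is assumed.** This stands. No switching rate is given, and the upper figures need every contact-only family to stay reachable without limit. A reader might infer that such children typically sit at risk until 18. That would take a successful contact at least every 18 months for up to 15 years, and a failed re-contact sequence flags loss at about 3 months. It is the extreme case.

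**Attending without completing the instrument.** The article says "we anticipate an instrument completion rate of approximately 70–80% per visit", with the HAQL, BCS and BFS prioritised at each visit. That suggests mostly intermittent gaps. A child assessed later has the event dated late, not missed, so this route is weaker than permanent loss of assessment.

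**Remote surveys.** Surveys may be completed online, on paper or by telephone (Patient-reported outcomes; Data management), so some contacts may carry a BCS or BFS. This stands in part: the event is still defined at a clinic visit, and a bare call still maintains follow-up.

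**Weighting.** It would be too strong to say that the planned weights are irrelevant. The Missing data section names PRO non-response, alongside loss, as a reason for its censoring weights, and the details may be left to an analysis plan not shown. But the weighting is a sensitivity analysis and, as written, does not move the censoring date in the main analysis.

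**Distance.** A reader might infer that distance from the centre would appear to delay continence. The documents do not support this: distance is in neither continence Cox model. It appears in the loss-to-follow-up regression and among the imputation and weighting variables.

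**Disclosure.** Completeness is tabulated in every publication, and more than 40% missingness at an assessment point blocks model-based inference for that instrument there. This makes the problem visible without correcting it.

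**Conclusion.** The point holds. The stated censoring rule does not match how the primary event is ascertained. For children who do not return for assessment it can only lower the continence curve. That direction follows from the protocol's own rules; the size does not. Under assumed switching of 3–10% per year, a true 31% at age 10 is understated by about 1–5 points if contact-only periods average 2 years and by about 3.5–10 points if families stay reachable indefinitely. At age 5, the subject of the first interim analysis, the effect is under 2 points in the scenarios run. Distortion of the deprivation coefficient is conditional on contact-only follow-up differing by deprivation, which the article does not quantify.

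A reader might infer that changing the censoring date fully restores the true curve. With the confirmation rule it does not, so both need attention.

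**What to change.** In Outcome measures and Loss to Follow-Up:

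1. For the continence endpoint, censor every child without an event at the date of the last scorable BCS (ARM) or BFS (HD), whatever the reason follow-up ended.
2. State how a single positive at the last assessment, never confirmed, is handled. One option is to date the event at the confirming visit. This removes the bias from unconfirmed positives but changes the quantity to confirmed continence by a given age: in the first model, 0.35 × 6/8 = 26.3% at age 10. The other option is an interval-censored analysis.
3. Keep the 18-month any-contact rule for the loss-to-follow-up outcome only.

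The cost is a few sentences. Assessment dates are already collected, and no formal analysis has yet been done. Nominal person-time falls. Drop-out related to continence itself is not cured, so the planned weighting is still needed, with leaving assessment as the censoring event.

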## Methods and analysis

### Study design

This study follows a longitudinal, prospective observational design. The registry has no anticipated completion date; patients are recruited on a continuous basis and followed until they reach 18 years of age. Fig 1 summarises the registry workflow, from identification of eligible patients through consent and baseline data capture to the schedule of longitudinal follow-up assessments and the definitions applied at censoring.

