### Study population and setting

Eligible paediatric patients (aged 0–17 years) with documented diagnoses of HD or ARM are invited to participate at the COCOE clinic, Montreal Children's Hospital. Prospective patients are identified through weekly reviews of colorectal clinic schedules.

Although HD and ARM are embryologically distinct conditions with different surgical approaches and long-term outcome profiles, both require lifelong multidisciplinary follow-up and are managed by the same specialist team at COCOE. Enrolling both conditions within a single registry infrastructure reflects this shared clinical pathway and the impracticality of maintaining two separate registries at a single centre. To respect these clinical and methodological distinctions, primary and multivariable analyses will be conducted separately for each disease cohort rather than pooled, with disease-specific instruments and predictors as detailed in the Statistical Analysis section.

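### Loss to follow-up is modelled as ever-lost versus retained without regard to observation time, and the two rules for flagging loss conflict

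*Protocol article*

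**What the plan says.** The Loss to Follow-Up section defines loss as no encounter, survey or contact "for 18 or more consecutive months in a participant aged under 18 years who has not yet transitioned to adult care". It then fixes the analysis: "Factors independently associated with the loss will be examined using logistic regression (ever-lost vs retained) as a secondary analysis". Table 2 (Outcome measures) repeats the choice: "Logistic regression (ever-lost vs retained); descriptive LTFU rate". The listed candidate predictors are diagnosis type, age at enrolment, sex, severity category, deprivation quintile and distance from the centre.

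Entry is staggered and observation has a ceiling. Under Study design, "patients are recruited on a continuous basis and followed until they reach 18 years of age", and under Study population and setting children may enter at any age from 0 to 17. The timeline puts the multivariable analyses in years 4 and 5, with enrolment still open.

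The protocol gives two times for the flag. Table 2 has "Flagged at 18-month mark; reviewed at each annual analysis". The re-contact procedure, whose last step is at 3 months after a missed visit, ends differently: "If no successful contact is made after this full sequence, the participant will be flagged as lost to follow-up in REDCap".

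**The concern.** A binary ever-lost outcome is interpretable when everyone has been observed for about the same time. Here observation runs from weeks to years, and part of the cohort cannot have the event at all. If those children count as retained, a predictor related to length of observation can appear to be associated with loss when it is not. Age at enrolment is such a predictor, because it sets how much time remains before 18.

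This analysis is what serves objective 5 (factors contributing to loss) and secondary outcome 5. The same table gives enterocolitis and reoperation, which accrue under the same staggered entry, Cox and Fine-Gray models. The inverse probability weighting that the protocol describes is a sensitivity analysis for the survival and longitudinal models and does not correct this one.

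The two flag rules raise a separate question: which children are coded as lost in the first place.

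**Working it through.** **1. The plan's accrual figures.** Incident 5 and re-engaged 3 per month: (5 + 3) × 12 = 96 a year; 96 × 5 = 480 over five years; 480 + 200 backlog = 680. These match the sample size section. The plan gives no expected loss rate, so any hazard below is an assumption.

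**2. Who cannot meet the definition.** Let w be the smaller of (data cut − enrolment) and (18 − age at enrolment), in years. Enrolment is itself a contact, so loss needs w ≥ 1.5. From entry date alone, the last 18 months of the continuous streams contribute 1.5 × 96 = 144 children who cannot be lost:

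- Year 5: 144/480 = 30%. With a backlog of 175 (middle of 150–200), all entered earlier: 144/(480 + 175) = 22%.
- Year 3: 144/288 = 50%, backlog left out.

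Children enrolled after age 16.5 come on top. Allowing for both limits, simulation gave 27–32% of the retained group at year 5 unable to meet the definition.

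**3. Unequal opportunity among the rest.** With a constant hazard h of last contact, the same for every child, P(ever-lost) = 1 − exp(−h × (w − 1.5)):

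| w (years) | h = 0.05 | h = 0.08 |
|---|---|---|
| 1.5 or less | 0 | 0 |
| 3 | 0.07 | 0.11 |
| 5 | 0.16 | 0.24 |

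The children differ only in how long they were observed.

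**4. Effect on age at enrolment.** Null simulation: no predictor affects the hazard. Assumptions: 60 incident children a year aged 0–1; 36 re-engaged a year aged 1–17.9; a backlog of 175–200 aged 0–17.9; ages uniform; hazard 5–10% a year; nominal 5% test. A child is lost if last contact + 1.5 years falls before the cut and before age 18.

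| | Year 5 | Year 10 |
|---|---|---|
| Logistic, odds ratio per 5 years of age | 0.87–0.98 | about 0.8 |
| Logistic, false positives | 1–21% | 79–99% |
| Cox time to loss, hazard ratio | about 1.0 | about 1.0 |
| Cox time to loss, false positives | 2–9% | 2–9% |

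The year-5 odds-ratio range reflects how fast the backlog enters: 0.98 if all in year 1, about 0.90 over three years, 0.87 over four. If it enters evenly over all five years the odds ratio is 0.83–0.84. The direction is towards older children appearing less often lost, because the age-18 ceiling shortens their window. A covariate unrelated to observation time kept a 4–5% error rate at year 5 under the logistic model.

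**5. The two flag rules.** If the last contact was the previous annual visit, the next visit is missed at month 12 and the sequence ends at 12 + 3 = month 15. A child who reappears between months 15 and 18 is lost under the re-contact rule and not lost under the definition and Table 2.

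**The case against.** Three objections carry weight.

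First, the article does not define retained or the analysis set for this model. A separate analysis plan could require a minimum follow-up. That would remove the children who cannot be lost, but it would leave unequal windows among the rest unless a fixed horizon were also set. What the article does fix, in two places, is a binary outcome with no time element; the timing of loss is only described.

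Second, a reader might infer that objective 5 would broadly yield spurious factors. The documents do not support that. Sex, diagnosis, severity, deprivation and distance are affected only if they vary with entry date or enrolment stream, and nothing in the protocol shows that they do.

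Third, a reader might expect older backlog children, enrolled early, to look more often lost. The simulation does not bear this out: even with the whole backlog in year 1, the age odds ratio is about 0.98. Backlog against incident stream then shows an odds ratio of about 2.2, but stream is not a listed predictor. That figure falls to 1.03–1.06 if the backlog enters over four years, and the year-1 milestone asks only for at least 25% of it.

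Also, month 15 assumes no survey or call since the previous annual visit. A later contact makes the gap at flagging shorter still, so the conflict stands.

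**Conclusion.** The point holds in a limited form. The logistic model mixes risk of loss with opportunity to be lost, and a substantial group (30% of the continuous streams at year 5, from entry date alone) cannot have the event. The bias is built in for age at enrolment. It is modest at the planned year 4–5 report and strong by year 10, which lies beyond any stated milestone but within the life of a registry with no end date. The 30% is arithmetic on the protocol's accrual figures. The odds ratios and false-positive rates rest on an assumed constant hazard and an assumed age mix, neither of which the protocol gives.

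The conflict between the flag rules is plain from the text and needs no assumption about rates. Both should be corrected, in proportion: this is one secondary analysis of the fifth-ranked secondary outcome.

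**What to change.** In Table 2 and the Loss to Follow-Up section, replace the logistic model with a time-to-loss model (Cox or discrete-time hazard) from enrolment, with the same predictors. The event occurs when 18 months without contact is reached. Censor at data cut, age 18, transition, death or withdrawal. Report loss per person-year or as cumulative incidence.

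Reconcile the two flag rules so that the analysis outcome uses one definition; the end-of-sequence flag could stay as a provisional operational marker.

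The cost is protocol wording: the contact log and date of last confirmed contact are already recorded, and no formal analysis has been run. One small downside should be stated. Under Confidentiality and data governance, clinical data of withdrawn children are destroyed, so these children may have to be left out rather than censored.

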## Objectives

The objectives of the COCOE Registry are: 1) to establish the first prospective registry of paediatric patients with HD and ARM in Canada; 2) to collect and analyse longitudinal data on incidence, clinical outcomes, and treatments; 3) to collect patient-reported outcomes on well-being, quality of life, and familial stress and functioning; 4) to improve understanding of regional variations in care and outcomes; and 5) to identify factors contributing to loss to follow-up.

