### Sample size and expected enrolment

The registry is designed for indefinite, continuous enrollment. We distinguish two enrollment streams: incident cases (children newly diagnosed with HD or ARM presenting to COCOE, estimated at a minimum of 5 per month) and previous cases (patients previously diagnosed but lost to follow-up and re-engaged, estimated at approximately 3 per month). Combined, the registry aims to enroll approximately 96 participants per year. Based on a prevalent backlog of an estimated 150–200 patients currently followed at COCOE, total enrollment over 5 years is projected at 480–680 participants.

While no minimum sample size is required for registry operation, we provide a feasibility projection. Based on published ARM cohort data reporting approximately 24–30% achieving full fecal continence [14], and HD cohort data reporting approximately 39% achieving a BFS ≥ 17 by adolescence, we project a combined continence event rate of approximately 30–35% within the first 5 years of registry operation [21]. This corresponds to approximately 145–240 continence events across the projected 480–680 enrolees, supporting inclusion of up to 14–24 covariates in the primary Cox model at an events-per-variable (EPV) threshold of 10 [22]. Importantly, this time-to-event framing includes all enrolled participants regardless of age at enrollment, resolving the limitation of the age-5 cross-sectional design by allowing older prevalent cases to contribute person-time and events from their enrolment date. Pre-specified multivariable analyses will be triggered only once this EPV threshold is confirmed at interim review; otherwise analyses will be limited to descriptive and unadjusted comparisons.

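### The loss-to-follow-up model lists age at enrolment but not prior loss, although about 3 in 8 planned monthly enrolees are re-engaged after an earlier loss, so age may absorb part of any prior-loss effect

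*Protocol article*

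**What the plan says.** The fifth aim in the Objectives section is "to identify factors contributing to loss to follow-up". The analysis that serves it is in the Loss to Follow-Up section: a secondary logistic regression comparing participants ever lost with those retained. Its candidate predictors are "diagnosis type, age at enrollment, sex, aganglionosis length or ARM Krickenbeck category, area-level deprivation quintile, and distance from COCOE". The list is introduced as including these variables, so it is not strictly closed.

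The section on sample size and expected enrolment separates two streams. Incident cases are "estimated at a minimum of 5 per month". Previous cases are "patients previously diagnosed but lost to follow-up and re-engaged, estimated at approximately 3 per month". The same paragraph mentions a third source, a backlog of an "estimated 150–200 patients currently followed at COCOE".

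Neither enrolment stream nor prior loss appears in the predictor list of the loss model, or in the lists for the time-to-event models under Statistical analysis. The nearest variable is a count of earlier missed appointments. The Missing data section names it as an auxiliary variable for imputation and carries it into the inverse-probability-of-censoring weights, which are a sensitivity analysis. It is not listed for the loss regression.

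**The concern.** One enrolment stream is defined by a past episode of the very kind of event the loss model is meant to explain. Prior loss is a natural candidate predictor of later loss. The document itself treats past missed appointments as informative about non-response, yet the one model intended to explain loss does not list that variable or anything equivalent.

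Age at enrolment is listed and probably tracks stream: newly diagnosed children are mostly very young, and children re-engaged after an earlier loss are likely to be older. If prior loss raises the risk of a further loss and is left out, the age coefficient can pick up part of its effect. A reader of the results might then direct retention effort by age when the useful marker is a history of disengagement. Even with no distortion of the age estimate, the model would leave out a plausible and actionable predictor.

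**Working it through.** **Enrolment arithmetic.** Inputs are from the sample size section: 5 incident and 3 re-engaged children per month, and a backlog of 150–200.

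- Annual enrolment: (5 + 3) × 12 = 96. This reproduces the stated figure ("the registry aims to enroll approximately 96 participants per year").
- Five years without backlog: 96 × 5 = 480. With backlog: 480 + 150 = 630 and 480 + 200 = 680. The ends of the stated range ("total enrollment over 5 years is projected at 480–680 participants") are therefore no backlog and the full 200.
- Re-engaged share of the monthly flow: 3 / 8 = 37.5%. Because 5 incident cases is a minimum, the share is lower if more arrive.
- Re-engaged children over five years: 3 × 12 × 5 = 180. Shares: 180 / 480 = 37.5%; 180 / 630 = 28.6%; 180 / 680 = 26.5%.

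**Illustrative simulation.** Everything below except the numbers of children is an assumption. Each run had 300 incident, 180 re-engaged and 0, 150 or 200 backlog children. Age at enrolment was mostly under 2 years for incident cases, uniform over 2–16 years for re-engaged and uniform over 1–16 years for backlog. Baseline loss was 15%, follow-up was equal, and age had no true effect. Ever-lost was regressed on age alone, then on age plus a re-engaged indicator, with 200 runs per scenario. The other five listed predictors were not simulated.

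Age odds ratio per 5 years without the indicator (share of runs with p < 0.05 in brackets):

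| Prior-loss OR | No backlog | Backlog 150 | Backlog 200 |
|---|---|---|---|
| 1 | 1.00 (3%) | 1.00 (4%) | 0.99 (4%) |
| 1.5 | 1.20 (38%) | 1.09 (16%) | 1.09 (15%) |
| 2 | 1.34 (72%) | 1.17 (33%) | 1.15 (31%) |
| 3 | 1.55 (97%) | 1.29 (81%) | 1.26 (75%) |

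With the indicator added, the age odds ratio was 0.98–1.00 with backlog and 1.00–1.06 without.

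**Unequal time at risk.** The simulation was repeated with staggered entry over five years (backlog in the first two), exit at year 5 or age 18, no loss countable in the first 18 months, and a baseline loss rate of 0.06 per year. After adding the indicator, the age odds ratio was 0.87–0.94 without backlog and 1.14–1.19 with it. It departed from 1 even when prior loss had no effect (0.94 without backlog; 1.18–1.19 with). That residue comes from follow-up time, not from stream.

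**The case against.** Several points on the other side stand.

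- The distortion is conditional. Re-engaged children must be older and prior loss must raise the risk of new loss, and the document gives no figure for either. If prior loss has no effect, the age odds ratio stays at about 1.00.
- Backlog children are probably also older at enrolment but were not lost. This loosens the link between age and stream and roughly halves the effect at a prior-loss odds ratio of 2.
- A partial proxy, earlier missed appointments, is already in the imputation and censoring-weight models. A reader might infer that prior disengagement is ignored throughout the plan; it is not.
- Prior loss may itself result from distance or deprivation, which are listed predictors. Adjusting for it could remove part of what the fifth objective seeks, so leaving it out of one version of the model is defensible.
- The predictor list is open, and an analysis plan not shown could extend it. That makes the addition easy, but nothing in the article commits to it.

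A reader might also infer that re-engaged children become cases by construction because they were once lost. The text does not support this. The definition concerns registry participants who have not withdrawn, the flag follows a re-contact sequence run by registry staff, and contact attempts are logged as they occur. All of this points to loss after enrolment, although no sentence says so outright.

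**Conclusion.** The point holds as a modest, conditional one. The loss model omits a baseline variable that defines an enrolment stream, that probably goes with a listed predictor, and that is close to the outcome being explained. If re-engaged children are older and more prone to a second loss, part of that effect may be attributed to age at enrolment. At a prior-loss odds ratio of 2 with equal follow-up, the size is about 1.15–1.17 per 5 years with the backlog and 1.34 without. These figures rest on assumed ages and loss rates and on a model holding only age.

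The stronger reading, that age at enrolment will emerge as a cause of loss, is not supported. The plan promises factors independently associated with loss, the two conditions are unquantified, and with the backlog at that odds ratio age reached p < 0.05 in only about a third of runs. This is an inexpensive improvement to a secondary analysis, not a defect that threatens the primary one.

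**What to change.** 1. Add an indicator of prior loss, or enrolment stream in three levels (incident, re-engaged, backlog), to the predictors of the loss regression.
2. Add the same indicator to the censoring-weight model, beside the missed-appointments variable already there.
3. Report the loss regression with and without the indicator, because prior loss may lie downstream of distance or deprivation.
4. State in one clause of the loss definition that only losses after enrolment count.

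The cost is one degree of freedom for a prior-loss indicator or two for the three-level stream, plus recording the recruitment route at enrolment. The study timeline says no formal analysis has yet been done, so the change would still be pre-specified. It does not deal with unequal time at risk in an ever-lost versus retained outcome, which needs separate handling before the age coefficient is interpreted.
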